### Outcomes

Table 1 presents an overview of the collected data and the study time path.

**Table 1 T1:** Collection of data and time path

**Topic**	**Instrument**	**Baseline**	**Follow-up**		
		**T0**	**T1**	**T2**	**T3**
			**3 months**	**6 months**	**12 months**
**Primary outcome**					
Full RTW	Registration system of the occupational health care service	X	X	X	X
**Personal characteristics**					
Gender, age, level of education, diagnosis by OP, sick leave in the previous year, history of mental disorders, expectations about full RTW.		X			
**Work characteristics**					
Type of function, number of working hours, contract type.		X			
Job content	JCQ	X	X	X	X
**Secondary outcomes**					
Partial RTW	Registration system of the occupational health care service	X	X	X	X
Total numbers of sick leave days	Registration system of the occupational health care service	X	X	X	X
CMD symptoms	4DSQ	X	X	X	X
Burnout symptoms	UBOS	X	X	X	X
Workability	3 questions of WAI	X	X	X	X
**Additional outcomes**					
Coping	Shortened 19-item version UCL	X	X	X	X
Self-efficacy	RTW-SE	X	X	X	X
Remoralization	RS-12	X	X	X	X
Experienced barriers, facilitators and social support for RTW		X	X	X	X
Experience and satisfaction with OP	Adapted version PSOHPQ	X	X	X	X
Experience and satisfaction with supervisor		X	X	X	X
**2 months after inclusion**					
Experiences supervisor					
Contact with worker, sick leave worker, work adaptations, contact with OP, CMD and sick leave, policy on sick leave and RTW			X		
Personal characteristics supervisor			X		

#### Primary outcome

The primary outcome is the time to full RTW. For this purpose the number of calendar days between the first day of sickness absence due to CMD and the first day of full RTW is calculated. Working the same hours as prior to the sickness absence in own or equivalent work for at least 4 weeks is considered full RTW. This means that reporting sick within 4 weeks of full RTW is not considered as a new period of sickness absence.

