### Study design

The study is designed as a two-armed cluster RCT with randomisation at the OP level (Figure 1). All participating OPs are recruited from a large collaborating OHS in the Netherlands. The OPs are randomised to an intervention group or a control group. Using an innovative training, OPs in the intervention group are trained to counsel sick-listed workers according to the Dutch national guideline ‘Management of mental health problems of workers by occupational physicians’. OPs in the control group receive no training and counsel sick-listed workers with care as usual. Workers are invited by the OHS after their first meeting with the OP. Data on sick leave and RTW of all invited workers are anonymously extracted from the registration system of the OHS during 1-year follow-up. In addition, in case of consent the worker receives a questionnaire at baseline (T0), and at 3 months (T1), 6 months (T2) and 12 months (T3) post baseline. In addition, 2 months after baseline a short questionnaire is sent to their supervisor.

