### Intervention

#### Intervention/guideline-based care

The Dutch guideline ‘The management of mental health problems of workers by occupational physicians’ promotes an activating approach of the OP as case and care manager to enhance the problem-solving capacity of the workers to achieve RTW. The guideline is based on cognitive behavioural principles to enhance the problem-solving capacity of workers in relation to their work environment, and process-based evaluation.

The guideline consists of four consecutive steps:

1) Problem orientation and Diagnosis: an early involvement of the OP is promoted (first assessment and start of counselling about 2 weeks after the worker reported sick). A simplified classification of mental health problems is introduced in four categories: i) Stress-related complaints, ii) depression, iii) anxiety disorder, and iv) other psychiatric disorders. Furthermore, problem inventory should focus on factors related to the worker and their work environment and the interaction between these two.

2) Intervention/Treatment: the OP acts as case manager by monitoring and evaluating the process of recovery (process-based evaluation). When recovery stagnates OPs should intervene by acting as care manager by using cognitive behavioural techniques to enhance the problem-solving capacity of the worker, providing the worker and work environment with information/advice on the recovery and the RTW process, contact the general practitioner when problems remain the same or increase, and refer the worker to a specialised intervention when necessary. In addition, the OP should advise the work environment (e.g. supervisors, managers, human resource managers) how to support the worker and enhance the recovery and RTW process.

3) Relapse prevention: Integration of relapse prevention from the first contact with the worker by enhancing the problem-solving capacity of the worker.

4) Evaluation: During follow-up meetings evaluation of the recovery process includes the perspectives of the worker, supervisor, and other involved professionals. Follow-up meetings with the worker should take place every 3 weeks during the first 3 months, and then every 6 weeks thereafter. The supervisor or work environment should be contacted once a month. Follow-up contacts with the general practitioner or other professionals should take place when the recovery process stagnates or when there is doubt about the diagnosis or treatment.

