#### Content of the training

OPs participating in the study and allocated to the intervention group received training in the guideline before the start of the study. This training was specifically designed for the purpose of this study and consisted of 8 meetings within 12 months. Each meeting took 2 h and was provided in groups of 4-6 OPs under the guidance of a trainer. The aim of the training was to enhance guideline adherence of the participating OPs by focussing on barriers that prevent OPs from using the guideline and finding solutions to overcome these barriers. This is considered to be a successful strategy for the implementation of guidelines [15,16].

During the 8 meetings the (key) recommendations within each consecutive step of the guideline were discussed. These discussions first focussed on barriers that would hinder OPs from using the specific recommendation in practice. The analysis of barriers was structured and based on an existing framework of barriers [17]. According to this framework guideline adherence can be affected by three main categories: 1) knowledge-related barriers (lack of awareness and lack of familiarity), 2) attitude-related barriers (lack of agreement, lack of self-efficacy, lack of outcome expectancy and lack of motivation/inertia of previous practice) and 3) external barriers that hinder physicians to apply the guideline in practice (guideline factors, environmental factors and patient factors). Second, the OPs in the group were invited to suggest solutions to address the perceived barriers taking into account the context of their daily practice. Third, the OPs drew up an action plan of how to implement these solutions in their daily practice, and agreed on learning objectives and ‘homework’ assignments. Between the meetings (a period of about 6 weeks) the OPs practiced the suggested solutions to experience if and how these would help to apply the guideline recommendations. During the next meeting the experiences of the OPs were evaluated and, when necessary, the solutions were adjusted to what the OPs had experienced in practice. This cycle of plan-do-check-act was repeated in each meeting for all the recommendations stated in the guideline.

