### Recruitment of participants

The study is conducted in the southern part of the Netherlands. The workers eligible for this study are on sick leave due to CMD diagnosed by the OP, counselled by an OP participating in the study, have had a first meeting with the OP, and are aged 18–65 years. From all eligible workers data on sick leave and RTW will be extracted from the registration system of the OHS anonymously.

Workers eligible for the data collection by means of the questionnaires work at one of the ± 320 companies served by this collaborating OHS that gave permission to invite their workers. The companies vary in size and serve different sectors. These workers are selected from the registration system of the OHS after their first consultation with the OP. They are sent an invitation letter from the OHS, as well as written information about the study. Workers who do not want to be contacted further can indicate this on a reply card. All eligible participants are contacted for additional information, and to check the inclusion and exclusion criteria. If the worker is willing to participate in the study and meets all the selection criteria, an informed consent and the baseline questionnaire will be sent to the worker.

Inclusion criteria for this study are: 1) CMD is the primary reason for sick leave diagnosed by an OP according to the Dutch Classification of Diseases (CAS) which is based on the ICD-10, 2) on current sick leave when selected from the registration system of the OHS after the first meeting with the OP, and 3) adequate command of the Dutch language. Exclusion criteria are: being suicidal, and a physical problem being the primary reason for sick leave at the time of study inclusion.

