#### Secondary outcomes

•Partial RTW is defined as the number of calendar days between the first day of sickness absence due to CMD and the first day of RTW, irrespective of the number of working hours per week.

•Total number of calendar days of sick leave is calculated for the 1-year follow-up period.

•CMD symptoms are measured by the Four Dimensional Symptoms Questionnaire (4DSQ), a self-report questionnaire measuring the four dimensions of common psychopathology: distress, depression, anxiety and somatisation. The 4DSQ consists of 50 items (each scored on a 5-point scale) and refers to symptoms during the past week. The 4DSQ has good psychometric properties [18].

•Burnout symptoms are measured by the Utrechtse Burnout Scale-General Survey (UBOS) [19], which is the Dutch version of the Maslach Burnout Inventory (MBI). The UBOS is a self-report questionnaire which measures three subscales: emotional exhaustion, mental distance, and competence. Higher scores on exhaustion and distance and lower scores on competence indicate burnout. The UBOS is a reliable and valid instrument [20].

•Workability is measured by three questions (items 1, 2, 3) of the shortened version of the Work Ability Index (WAI) [21,22]. The WAI is a self-report questionnaire and is a reliable and valid instrument [23,24].

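### Return-to-work time counts from day 1 of absence but workers enter only after a first OP meeting: if training brings that meeting forward, the intervention arm looks faster with no true effect

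*Protocol article*

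**What the plan says.** **Time origin.** In the Protocol article, Primary outcome, "the number of calendar days between the first day of sickness absence due to CMD and the first day of full RTW is calculated". Partial return has the same origin (Secondary outcomes section): "Partial RTW is defined as the number of calendar days between the first day of sickness absence due to CMD". Its event is a return to work at any number of hours.

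**Entry.** Under Recruitment of participants, the eligible workers, including those whose data come only from the registration system, must be "counselled by an OP participating in the study, have had a first meeting with the OP, and are aged 18–65 years". Study design agrees: "Workers are invited by the OHS after their first meeting with the OP". A later inclusion criterion in the recruitment section adds being "on current sick leave when selected from the registration system of the OHS after the first meeting with the OP".

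**Link to the intervention.** The guideline promotes "first assessment and start of counselling about 2 weeks after the worker reported sick" (Intervention/guideline-based care). On the training, the article says: "This cycle of plan-do-check-act was repeated in each meeting for all the recommendations stated in the guideline". Care as usual describes control adherence as low. OPs are randomised, not workers, so a worker enters through an OP whose arm is already set.

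**Analysis.** Statistical analysis names survival methods for full and partial return-to-work (RTW) that allow for clustering within OPs, with adjustment for baseline differences if needed. It does not say when a worker joins the risk set.

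**The concern.** From day 1 of absence to entry, an included worker cannot have the primary event. Anyone who returns fully in that interval and is never seen by the OP is not in the study. This is immortal time, and its length depends on the date of the first meeting, which comes after randomisation and which the intervention aims to shorten.

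If the intervention arm meets earlier, it carries less event-free time and takes in more short absences. A comparison from day 1 then mixes entering earlier with returning earlier. Neither the clustering term nor baseline adjustment removes this. At stake are the primary HR and its type I error.

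Partial RTW has the same origin and a further problem. A worker can be partly back while still sick-listed, so the event may already have happened before the OP first saw the worker.

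**Working it through.** **Inputs from the article.** Control RTW is 55% at 3 months and 75% at 6 months (Sample size). The total is 232 workers, so 116 per arm. Follow-up is 1 year. The guideline's first assessment is at about 2 weeks.

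**Inputs assumed.** Mean entry day by arm, and its spread (SD 7 days). The article gives neither.

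**The plan's own figure.** The sample size reproduces closely. With 3.5–4 workers per OP, the design effect is 1 + (m − 1) × 0.025 = 1.0625–1.075. Then 89 × 1.0625–1.075 = 95–96 per arm (stated 97), 100 × the same = 107–108 (stated 110), and 220/0.95 = 232. This point does not affect it.

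**Step 1: hazards from the control curve, with 91 days per quarter.**
- First 3 months: −ln(0.45)/91 = 0.00877 per day.
- Next 3 months: ln(0.45/0.25)/91 = 0.00646 per day.

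**Step 2: what entry does when both arms follow this one curve.** For entry at day s, the share back before entry is 1 − exp(−0.00877 s). RTW by 3 months among those enrolled is 1 − 0.45/exp(−0.00877 s).

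| Entry day | Back before entry | RTW by 3 months among enrolled |
|---|---|---|
| 21 | 17% | 46% |
| 28 | 22% | 42% |
| 35 | 26% | 39% |
| 42 | 31% | 35% |

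With entry at day 21 against day 35, the enrolled arms show 46% against 39% although nothing differs but the entry date.

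**Step 3: simulation under the null.** True HR 1, 116 per arm, no clustering, inclusion only if RTW falls after entry, censoring 365 days after entry, Cox model. An HR above 1 means faster RTW in the intervention arm. Ranges cover separate runs; the smallest had 600 trials, for which a rejection rate of 8% has a 95% interval of about 6–11%.

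| Mean entry day, intervention vs control | HR, at risk from day 1 | Type I error |
|---|---|---|
| 28 vs 28 | 1.00 | 4–5% |
| 28 vs 35 | 1.07–1.08 | 7.5–10% |
| 21 vs 35 | 1.13–1.15 | 14–17% |
| 21 vs 42 | 1.20–1.22 | 27–30% |

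With entry date as delayed entry, the HR is 1.00–1.01 and type I error 4–7% in these scenarios.

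**Step 4: sensitivity to the shape of the curve.** Four distributions were used (Weibull, lognormal, a Weibull shifted by 14 days, exponential), with 110 per arm and the intervention meeting at mean day 14.
- Control at day 21: HR 1.07–1.11, type I error 7–12%.
- Control at day 28: HR 1.13–1.20, type I error 14–26%.
- Control at day 42: HR 1.26–1.41, type I error 38–68%.
- Delayed entry: HR 0.99–1.01, type I error about 5% throughout.

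Restarting the clock at the first meeting is only a partial remedy: in the Weibull case the null HR was still 1.03–1.10.

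**The case against.** **The gap is not shown.** A reader might infer that the training does bring first meetings forward and that the primary HR is therefore biased. The article does not support that. It shows that the training aims at an early first meeting, not that it achieves one. Control OPs are expected to follow the same guideline, compliance was minimal after an earlier three-day training, and the low adherence reported is not tied to the 2-week item. This stands: with equal timing there is no bias, and earlier control meetings would reverse its direction.

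**Still being sick-listed at selection.** A reader might also take this as a condition on every worker. The article applies the first-meeting condition to the registry data, but lists current sick leave at selection later, after the text on questionnaire recruitment. Whether it binds the registry cohort is unclear. The concern needs only the first condition.

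**Calibration.** The 55% and 75% are planning figures for workers in the control group, whereas Steps 1–3 apply them to all absences from day 1. That is fair, but it does not help the plan. Calibrating the 55% to enrolled workers makes the bias larger: day 21 vs 35 gives HR 1.22 and rejection of 30%.

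**Left to an analysis plan.** An unseen plan may specify delayed entry, and nothing in the article excludes it. The day-1 origin is not wrong in itself. But the article fixes the origin, the entry rule and the link to the intervention, and together they produce the problem unless entry time is modelled.

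**The remedy is not exact.** It assumes that entry date is unrelated to prognosis. When control entry depended on prognosis (day 21 vs 35), the null HR under delayed entry was 0.94 or 1.06. It also leaves RTW gained before entry outside the HR, although earlier contact is part of guideline-based care. Both points stand and belong with the fix.

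**Conclusion.** The concern holds conditionally. If first meetings come earlier in the intervention arm, a survival analysis with everyone at risk from day 1 makes that arm look faster with no true effect. Under the null with the protocol's control curve, a gap of 1 week gives an HR of about 1.07 and type I error of about 8%; 2 weeks, about 1.14 and 14–17%; 3 weeks, about 1.2 and 27–30%. With no gap there is no bias.

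These sizes rest on assumed entry dates, on RTW being the same in both arms, and on ignoring OP clustering, which at the planned ICC and cluster size should change type I error only slightly. Confidence is high for the mechanism and medium for its size in this trial. A trial meant to raise adherence should not depend on one named recommendation staying unchanged.

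**What to change.** 1. Keep days since the first day of absence as the time scale. Let each worker enter the risk set at the date of the first OP meeting, using a left-truncated Cox model with OP clustering. Wherever current sick leave at selection is applied, use the selection date as entry, and state whether that criterion applies to the registry cohort.
2. For partial RTW, leave out workers who had already partly returned before entry.
3. Report days from the sick report to the first OP meeting by arm as a separate process result. This shows any gap between the arms and any gain in earlier contact.
4. Check the assumption about entry date by repeating the analysis with adjustment for baseline prognostic factors.

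The cost is one extra registry date per worker and a short addition to the analysis section. The trade-offs are that RTW gained before entry is not in the HR, and that the correction is exact only if entry date is unrelated to prognosis given time absent.

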#### Secondary outcomes

•Partial RTW is defined as the number of calendar days between the first day of sickness absence due to CMD and the first day of RTW, irrespective of the number of working hours per week.

•Total number of calendar days of sick leave is calculated for the 1-year follow-up period.

•CMD symptoms are measured by the Four Dimensional Symptoms Questionnaire (4DSQ), a self-report questionnaire measuring the four dimensions of common psychopathology: distress, depression, anxiety and somatisation. The 4DSQ consists of 50 items (each scored on a 5-point scale) and refers to symptoms during the past week. The 4DSQ has good psychometric properties [18].

•Burnout symptoms are measured by the Utrechtse Burnout Scale-General Survey (UBOS) [19], which is the Dutch version of the Maslach Burnout Inventory (MBI). The UBOS is a self-report questionnaire which measures three subscales: emotional exhaustion, mental distance, and competence. Higher scores on exhaustion and distance and lower scores on competence indicate burnout. The UBOS is a reliable and valid instrument [20].

•Workability is measured by three questions (items 1, 2, 3) of the shortened version of the Work Ability Index (WAI) [21,22]. The WAI is a self-report questionnaire and is a reliable and valid instrument [23,24].

#### Prognostic measures

•Personal characteristics such as age, gender, level of education, sick leave in the previous year, history of mental disorders, and expectations about full RTW are measured at baseline.

•Work characteristics such as number of working hours, contract type, type of work, profession and job content are measured at baseline. Job content is measured with the Dutch version of the Job Content Questionnaire (JCQ) [25], a self-report questionnaire which measures the social and psychological characteristics of jobs. The JCQ assesses the following scales: psychological job demands, decision latitude, social support, physical demands and job insecurity.

#### Additional measures

Factors which can be influenced by the intervention and thereby can influence RTW are also measured. The results of these additional measures will be reported separately from the results of this RCT.

•Coping style is measured with the shortened 19-item version of the Utrecht Coping List (UCL) [26], a self-report questionnaire which measures coping behaviour. The 19-item version assesses the following scales: 1) active problem solving, 2) seeking social support, 3) palliative reaction pattern, 4) avoidance behaviour, and 5) expression of emotions.

•Self-efficacy with regard to RTW is measured by the RTW-SE for workers with mental problems. The RTW-SE is a self-report questionnaire which assesses the self-efficacy in the RTW process. The RTW-SE shows promising reliability, validity and prediction of actual RTW within 3 months [27].

•Remoralization (perception of recovery) is measured with the 12-item Remoralization Scale (RS-12). The RS-12 is a self-report questionnaire which indicates the level of morale in mental health care and has shown promising reliability and validity [28].

•Workers’ experiences with the consultations with their OP, and the contact with their supervisor, are measured. For example, the number and content of the consultations, and the topics of the conversations. Satisfaction with the counselling by the OP is measured with an adapted version of the Patient Satisfaction with Occupational Health Professionals Questionnaire (PSOHPQ) [29].

•Experiences of the supervisor are measured using self-formulated questions. This questionnaire includes topics such as the contact with worker and the OP, previous experience with CMD and sick leave in general, and policy on sick leave and RTW [see Additional file 1].

### Sample size

A power analysis was performed to determine the sample size needed to detect a difference between the control and intervention group with respect to the time workers fully return to their work (primary outcome measure). Proportions of full RTW were adopted from previous studies [7,30]. It was assumed that in the usual care (control) group 55% of the workers would have returned to work after 3 months and 75% after 6 months, whereas in the intervention group these figures would be 75% and 90%, respectively. With a power of 80% at a 0.05 alpha level, assuming an ICC of 0.025 and taking into account a correction factor for the clustered design, it was calculated that 2 × 97 workers would be needed to detect the difference after 3 months and 2 × 110 workers for the difference after 6 months. Allowing for 5% attrition on the sick leave data, a total of 232 workers need to be included.

